### Power and sample size calculation

Starting with a pilot study, we will include five people in each group. On this basis we will do power and sample size calculations in order to commence with the randomized controlled trial.

### Analysis

The primary outcome measure will be the score on the TGUG. Secondary outcome measures will include SEMG, strength of quadriceps and gluteus medius, OHS and SF-36 questionnaire score, score on the 5tSTS, the Trendelenburg test score and the 6MWT score. Normality of data will be checked via the Kolmogorov-Smirnov test. Differences between both treatment groups at baseline and follow-up measurements will be analyzed using the chi-square statistical method for categorical variables. For continuous variables, comparisons between both groups’ baselines will be made using an independent samples t-test. Comparisons between both groups at the follow-up measurements will be made using a two-factor repeated measures Analysis of Variance (ANOVA) (group × time). Baseline values will be included as the first follow-up measurements. Differences between successive measurements within a treatment group will be analyzed using a one-factor repeated measures ANOVA. Significance value for all tests is set at *P* <0.05. The results of all subjects will be analyzed, regardless of their treatment adherence (intention-to-treat analysis).

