#### Trendelenburg test

This test measures abductor force in a functional way. The patient is asked to raise one leg (sound side) and raise the non-stance side of the pelvis as high as possible for 30 seconds. The response is classified as followed [17]:Normal: The pelvis on the non-stance side can be lifted maximally for 30 seconds.The pelvis on the non-stance side can be lifted but not maximallyThe pelvis is elevated but not maintained for 30 secondsNo elevating of the pelvis on the non-stance sideDrooping of the pelvisNon-valid response: due to hip pain or uncooperative patient

Test-retest reliability coefficients (κ) are found to be greater than 0.75 [18].

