### Randomization, blinding and treatment allocation

Patients will be allocated to one of two treatment groups by the surgeon at the preoperative consultation. Randomization will take place by means of blinded envelopes. In total 10 envelopes are provided: five that allocate the patient to the AA group and five that allocate the patient to the PAA group. This is to ensure that the same number of patients is randomized in one of the two treatment groups. Patients receive the same information from the surgeon regardless of their group allocation. A blinded researcher will perform baseline and follow-up measurements. To ensure blinded assessment, SEMG will be carried out by an independent researcher. This because blinding is not possible due to different locations of scar tissue.

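### The Trendelenburg grades run from best to worst, but the stated chi-square test ignores that order and loses power for the question the trial asks

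*Protocol article*

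**What the plan says.** - **Scale.** The Trendelenburg test section introduces the classes with "The response is classified as followed". Five of them descend from a full pelvic lift held for 30 seconds to a pelvis that drops. A sixth is for a response that is not valid because of hip pain or lack of cooperation.
- **Role.** The Analysis section lists "the Trendelenburg test score and the 6MWT score" among the secondary outcomes. The primary outcome is the Timed Get-Up-and-Go (TGUG) test.
- **Test.** The same section states: "Differences between both treatment groups at baseline and follow-up measurements will be analyzed using the chi-square statistical method for categorical variables". It assigns t-tests and repeated measures ANOVA to continuous variables. It names no ordinal or exact test.
- **Alpha and population.** "Significance value for all tests is set at" 0.05. On the population: "The results of all subjects will be analyzed, regardless of their treatment adherence (intention-to-treat analysis").
- **Numbers.** The Power and sample size calculation section says: "Starting with a pilot study, we will include five people in each group". The size of the randomized trial is to be worked out from the pilot and is not given.
- **Question.** The Discussion hypothesizes a directional benefit: better or earlier function after PAA than after the anterolateral approach (AA).

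**The concern.** The other listed outcomes are EMG signals, forces, questionnaire scores, times and a distance. Only the Trendelenburg response is recorded in classes, so the chi-square rule for follow-up falls on it. This is a test the article states, not a detail it leaves open.

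Pearson's chi-square asks whether the two arms differ in any way across the classes. With five grades it spreads its sensitivity over 4 degrees of freedom. The trial's question is narrower: whether the PAA grades lie nearer the normal end. The protocol presents the Trendelenburg test as a functional measure of abductor force, so it bears directly on the muscle-sparing rationale. What is at stake is a real shift in grade being missed, or a significant result that does not show which arm did better.

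**Working it through.** The protocol states no power or effect size, so there is no figure of its own to reproduce.

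**Step 1: does chi-square ignore the order?** Take illustrative grade counts (best to worst) of 3,1,1,0,0 in one arm and 0,0,1,1,3 in the other. With equal arms, X² = Σ(a − b)²/(a + b).
- X² = 9/3 + 1/1 + 0/2 + 1/1 + 9/3 = 8 on 4 df, p = 0.092. Reordering the columns only reorders the sum, so p stays at 0.092.
- Rank-sum with mid-ranks: the first arm has 2 + 2 + 2 + 4 + 5.5 = 15.5 against an expected 27.5. The exact two-sided p is 4/252 = 0.016 (0.010 by the normal approximation). After one shuffle of the grades the normal-approximation p becomes 0.283.

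So the rank test responds to the order and chi-square does not.

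**Step 2: cost in power.** Inputs from the protocol: five valid grades, 1:1 allocation ("five that allocate the patient to the AA group and five that allocate the patient to the PAA group") and alpha 0.05. Assumed, because the protocol gives none: two-sided testing, the grade distributions, the effect size and the arm size.

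Assumed control distribution: 20/25/25/15/15%, cumulative 0.20, 0.45, 0.70, 0.85. A common odds ratio OR turns each cumulative proportion c into OR·c/(1 − c + OR·c).
- OR 3: 0.429, 0.711, 0.875, 0.944, so grades of about 43/28/16/7/6%.
- OR 2: 0.333, 0.621, 0.824, 0.919, so grades of about 33/29/20/10/8%.

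Simulated power (error of up to about two percentage points):

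| Odds ratio | Per arm | Chi-square | Rank-sum | Gap (points) |
|---|---|---|---|---|
| 3 | 30 | 42% | 65% | 23 |
| 3 | 50 | 65% | 86% | 21 |
| 2 | 30 | 18% | 31% | 13 |
| 2 | 50 | 28% | 48% | 20 |

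A second assumed pair (control 10/20/30/25/15%, treated 35/30/20/10/5%) gives 45% v 69% at 20 per arm, 66% v 86% at 30 and 91% v 98% at 50. The direction is the same, and the gap narrows once both tests have high power.

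**Step 3: the pilot's five per group.** The mean expected count over five grades is 10/(2 × 5) = 1.0. Full enumeration gives chi-square an actual size of about 2% against the nominal 5%: 0.020 with equal grades, 0.021 with the second control distribution. The error is therefore conservative. Power at this size under the second pair is 6% for chi-square and 20% for rank-sum, so neither is useful. With that control distribution chi-square's size recovers to 0.043 at 20 per arm, 0.044 at 30 and 0.047 at 50.

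**The case against.** **The link is an inference.** The chi-square sentence does not name the Trendelenburg score. If the score were reduced to normal against abnormal, the order would not matter. The inference still stands: the sentence covers follow-up, no other listed outcome is categorical, and no reduction to two levels is stated.

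**The order is not explicit.** The protocol says the response is classified and does not call it ordinal. The second class concerns the height of the lift and the third how long it is held, so their relative rank can be argued. The ends of the scale are plainly ordered and the list descends, which is enough for a rank method.

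**The magnitude is assumed.** This is true of the distributions, odds ratios and arm sizes. The loss appears in every setting tried, but its size varies.

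**Impact is limited.** The outcome is one of many secondary ones, and the Discussion says the test could be dropped to spare patients. This limits severity.

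Three stronger readings are tempting, and the document does not support them:
- *Non-valid responses are tested as a sixth grade.* The class is in the list and all subjects are to be analyzed, but nowhere is it said that a non-valid response enters the test as a level. Its handling may be set out in the full protocol or statistical analysis plan.
- *Chi-square is unreliable at the trial's numbers.* Five per group is the pilot size only. The error there is conservative, and it largely disappears from about 20 per arm.
- *Leaving out the baseline grade is an error.* An unadjusted comparison of randomized arms is valid. Adjustment is a gain in precision, not a correction.

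**Conclusion.** The point holds in a limited form. The stated test for the one graded outcome ignores the grading. It does not address the directional hypothesis, and in the main scenarios at 30 to 50 per arm it gives up about 13 to 23 percentage points of power. That size rests on assumed distributions and odds ratios of 2 to 3. That chi-square ignores order needs no assumption.

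Chi-square does not inflate the type I error in the settings examined. The primary TGUG analysis is untouched. This is a minor point and a cheap improvement.

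**What to change.** - Compare the five valid Trendelenburg grades at follow-up with an ordinal method: a Wilcoxon rank-sum test, exact when numbers are small, or a proportional-odds model with arm and baseline grade where it can be fitted.
- Report non-valid responses separately by arm, not as a grade. Give the reason only if it was recorded, because the list puts hip pain and lack of cooperation in one class.
- The Trial status section says recruitment finished in September 2014 and the trial is at statistical analysis. State that the test was changed and when. If results have been seen, report the chi-square result alongside.

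The cost is a short change to the analysis wording and a disclosure. No new data are needed. One small downside is that the odds-ratio summary assumes a roughly proportional shift across the grades.

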**Methods/Design:**

This study uses a prospective, randomized, parallel-group design with blinded assessment and unblinded treatment to compare the percutaneous assisted approach with the anterolateral approach in total hip replacement surgery. The postoperative results of patients operated on using the percutaneous assisted approach will be compared with those of patients operated on using the anterolateral approach. Prior to surgery patients will undergo baseline measurements. These will consist of gluteus medius measurements (surface-electromyography, strength measurements of abductors and quadriceps and the Trendelenburg test), questionnaires (Oxford Hip Score and 36-item Short Form Health Survey) and functional measures (the Timed Get-Up-and-Go test, Five times Sit-to-Stand test and Six-Minute Walk test). These measurements will be repeated four and 12 weeks after surgery. After surgery both groups will receive usual care.

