### Follow-up measurements

All measurements will be repeated at four weeks and three months post-surgery. Six weeks post-surgery patients will be seen by the orthopedic surgeon for clinical and radiographic control. These are routine measurements to assess the postoperative course.

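### The between-group ANOVA counts the pre-operative value as a follow-up, does not name the term that tests treatment, and never adjusts for baseline

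*Protocol article*

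**What the plan says.** The Analysis section of the protocol article sets the primary outcome: "The primary outcome measure will be the score on the TGUG". For continuous variables it then states: "Comparisons between both groups at the follow-up measurements will be made using a two-factor repeated measures Analysis of Variance", with group × time given in brackets. The next sentence reads: "Baseline values will be included as the first follow-up measurements".

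The timing is clear elsewhere. The abstract's Methods/Design paragraph says "Prior to surgery patients will undergo baseline measurements", and the section on follow-up measurements says "All measurements will be repeated at four weeks and three months post-surgery". The time factor therefore has three levels, one before surgery and two after it.

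The only other between-group use of baseline is an independent-samples t-test comparing the arms before surgery. No stated model has baseline as a covariate. The section does not say whether the group main effect or the group × time interaction is the treatment test.

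**The concern.** The stated aim of this analysis is to compare the arms at follow-up. A value taken before surgery is not a follow-up, and the surgical approach cannot have changed it. Entering it as an outcome level has different consequences for the two terms of the ANOVA:

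- **Group main effect.** It averages the arm difference over all three visits, one of which has a true difference of zero. The estimate shrinks toward zero, and any chance baseline difference is carried into it.
- **Group × time interaction.** Here baseline is the reference for change, so nothing is diluted. But the F test has 2 df and no direction, and it does not estimate the difference between approaches at 4 or at 12 weeks.

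Because the deciding term is not named, the primary result could rest on either, and their power can differ widely. Baseline TGUG, planned for every patient, is left unused as a covariate in both. The article fixes this choice itself, so it is not a detail left to a later analysis plan.

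**Working it through.** The article gives no sample size, power or target effect for the main trial, so there is no figure of its own to reproduce.

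**From the article:** three time levels, with no possible effect at the first; equal allocation (the randomization section: "This is to ensure that the same number of patients is randomized in one of the two treatment groups"); a 0.05 significance level, with sidedness not stated.

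**Assumed:** two-sided test; SD 1 at each visit; equal correlation ρ between visits (compound symmetry), tried from 0.3 to 0.8; n = 30 per arm; effect d = 0.6 SD at both follow-ups. The top of the ρ range is the TGUG reliability quoted in the Functional measures section (0.80), which comes from another population.

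**Step 1, dilution of the main effect.** With true differences (0, d₄, d₁₂), the main effect estimates (0 + d₄ + d₁₂)/3. The mean post-operative difference is (d₄ + d₁₂)/2. The ratio is 2/3, whatever the SD, ρ or pattern of follow-up effects.

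**Step 2, power at ρ = 0.5.**

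- *Main effect.* Variance of a patient's three-visit mean: (1+2ρ)/3 = 0.667. Non-centrality: 0.4/√[(2/30) × 0.667] = 1.90 on 58 df. Power 46%.
- *Interaction.* The effects (0, 0.6, 0.6) have mean 0.4 and squared deviations summing to 0.16 + 0.04 + 0.04 = 0.24. λ = (30/2) × 0.24/(1−ρ) = 7.2 on 2 and 116 df. Power 66%.
- *Joint baseline-adjusted test of both visits.* Given baseline, each visit has variance 1−ρ² = 0.75 and the two have covariance ρ−ρ² = 0.25. λ = 15 × (2 × 0.36)/(0.75 + 0.25) = 10.8 on 2 and 56 df. Power 83%.
- *ANCOVA on the mean of both follow-ups.* Variance (1+ρ)/2 − ρ² = 0.50. Non-centrality: 0.6/√[(2/30) × 0.50] = 3.29 on 57 df. Power 90%.

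A 10,000-run simulation of this case gave 46% (main effect), 65% (interaction) and 89% (ANCOVA on the mean).

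**Step 3, other correlations (sustained effect).**

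| ρ | Main effect | Interaction | Joint adjusted test | ANCOVA on follow-up mean |
|---|---|---|---|---|
| 0.3 | 55% | 51% | 78% | 86% |
| 0.5 | 46% | 66% | 83% | 90% |
| 0.7 | 40% | 87% | 93% | 97% |
| 0.8 | 37% | 97% | 98% | 99% |

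At ρ = 0.5, 80% power needs 66 per arm with the main effect and 22 with ANCOVA on the mean.

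**Step 4, other effect patterns at ρ = 0.5.** The Discussion's hypothesis allows a lasting benefit or merely a quicker recovery.

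| Pattern (week 4, week 12) | Main effect | Interaction | Joint adjusted test | ANCOVA on follow-up mean |
|---|---|---|---|---|
| d, d/2 | 29% | 53% | 66% | 68% |
| d, 0 | 15% | 66% | 70% | 37% |

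The joint adjusted test is at least as powerful as the interaction in all three patterns. ANCOVA on the mean is not.

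**The case against.** The strongest defence is that the only term the section prints is group × time, and that the Discussion expects one arm to improve more or sooner than the other. The interaction tests exactly that. Read this way, baseline is the reference for change and the dilution argument falls away. This stands. A reader might infer that the planned treatment effect is biased toward zero as such. The article does not support that, because it never names the main effect as the test.

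A reader might also infer that labelling baseline a follow-up makes false positives more likely. It does not: under randomization neither term has an inflated type I error from this source.

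Three further points limit the size of the problem:

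- The 90% figure belongs to the average of two follow-ups, so part of the gain comes from averaging. ANCOVA at a single visit has 75% power at ρ = 0.5 (65% if α is split over two visits), against 66% for the interaction. At ρ = 0.7 the figures are 89% and 83%, against 87%.
- For an early-only effect the interaction beats ANCOVA on the follow-up mean (66% against 37% at ρ = 0.5).
- At ρ near 0.8 the interaction loses very little under a sustained effect.

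These points argue for choosing the adjusted contrast with care. They do not rescue the main-effect reading, settle which term decides, or make the interaction yield a difference at each visit.

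**Conclusion.** The point holds in conditional form. Three parts come from the text alone: a pre-operative value is classed as a follow-up outcome, the deciding term is not named, and baseline is never a covariate.

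The consequence depends on the term read. For the group main effect, the one-third dilution is exact and needs no assumption beyond a zero expected difference before surgery. For the interaction there is no dilution; the cost is an undirected test, no visit-specific estimate, and lower efficiency that is marked at low or moderate visit correlation and slight at about 0.8.

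All power figures rest on the assumed arm size, effect, correlation structure and two-sided test. The only arm size in the article is the pilot's five per group, and the figures for 30 per arm should not be carried over to it.

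A group × time ANOVA that includes baseline remains a valid randomized comparison, so this is a matter that should be fixed, not one that invalidates the trial.

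**What to change.** Reword the Analysis section as follows.

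1. Use only the 4- and 12-week values as outcomes, in a linear mixed model with group, visit, group × visit and baseline TGUG as covariate. A constrained longitudinal model with a common baseline mean is an alternative. Keep the adjustment whatever the baseline t-test shows.
2. Name the primary contrast in advance: a joint test of both visits, or one named visit. The joint test suits a hypothesis that allows either a lasting or a faster benefit.
3. Report the adjusted PAA−AA difference with its 95% CI at each visit.
4. Apply the same model to the continuous secondary outcomes.

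This changes analysis wording only and needs no new data or patients. The Trial status section says recruitment has ended and the trial is at the analysis stage. The change should therefore be dated and made before the arms are compared. If they have already been compared, report it openly as a change alongside the planned ANOVA.

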## Discussion

The aim of this study is to assess the difference in functional outcome after THR through the PAA, compared to THR through the AA. The main difference between these two approaches is their impact on the gluteus medius. Whereas the AA detaches two thirds of the gluteus medius, the PAA only detaches a small part of the muscle. Since the gluteus medius is one of the most important muscles for the stability of the hip joint [10–12], we hypothesize that functional outcome is better or is achieved faster if THR surgery is performed through the PAA instead of the AA.

For this study we chose to have multiple outcome measures (SEMG, strength of gluteus medius and quadriceps, the Trendelenburg test score, the 6MWD and scores on the OHS, SF-36, TGUG and 5tSTS tests) to be certain we measure all possible effects. According to Vissers *et al*. three aspects should measure functional outcome: self-perceived function, functional tests in a laboratory setting and actual daily activity [4]. Both self-perceived function (measured by the OHS and SF-36 questionnaires) and functional tests (measured by the 6MWT and the TGUG, 5tSTS and tests) are use as outcome measures in our study. However, we chose not to assess actual daily activity at this stage. Rasch *et al*. reported remaining muscle atrophy up to two years after THR [5]. Therefore, we chose to include muscle strength measurements (measured by the SEMG, MicroFET and Trendelenburg tests). If this protocol takes too much effort for our patients it is possible that we could reduce it by removing the 6MWT and the Trendelenburg test.

This study has the following limitations. First, complete blinding cannot be achieved because of the SEMG measurements of the gluteus medius and the difference in location of scar tissue for both surgical approaches. Therefore, we chose to have an independent researcher carry out SEMG measurements and note the results, ensuring the other measures will be blinded. Second, we will only evaluate the short-term outcome. Because of the difference in approach we assume that the intervention group will already show a great deal of improvement in the short-term, while the control group will improve less. In later studies it will be necessary to investigate long-term success as well.

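### Within-arm ANOVAs and baseline tests at P<0.05 are added to a valid between-arm analysis without being labelled descriptive, a minor risk of misreading

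*Protocol article*

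**What the plan says.** The Analysis section of the protocol article names a single primary outcome: "The primary outcome measure will be the score on the TGUG". It then lists four procedures:

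- Categorical variables, between arms: "Differences between both treatment groups at baseline and follow-up measurements will be analyzed using the chi-square statistical method for categorical variables".
- Continuous variables, between arms before surgery: "comparisons between both groups’ baselines will be made using an independent samples t-test".
- Continuous variables, between arms after surgery: "Comparisons between both groups at the follow-up measurements will be made using a two-factor repeated measures Analysis of Variance (ANOVA) (group × time"). The baseline value enters this model as the first of the repeated measurements.
- Continuous variables, inside each arm: "Differences between successive measurements within a treatment group will be analyzed using a one-factor repeated measures ANOVA".

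One threshold covers them all: "Significance value for all tests is set at" P<0.05. No procedure is called descriptive, and no sentence says which of them carries the treatment conclusion.

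The Discussion gives the expected result: "the intervention group will already show a great deal of improvement in the short-term, while the control group will improve less". Measurements are taken before surgery, at four weeks and at three months (Follow-up measurements). The pilot has five patients per arm, and the size of the main trial is not given (Power and sample size calculation).

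**The concern.** The trial's aim is comparative: does PAA give better function than AA? Both arms receive a hip replacement and the same usual care. Change over time inside one arm therefore mixes recovery from surgery and relief of the hip complaint with any effect of the approach. A one-factor ANOVA in one arm cannot separate these, and running it in each arm does not turn the pair into a comparison.

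The usual trap is that one arm gives P<0.05, the other does not, and the reader concludes that the arms differ. The pattern is common even when they do not. The Discussion expects more improvement with PAA than with AA, so two parallel within-arm P values could easily be taken as confirming it. They could also disagree with the between-arm result, with nothing in the article to say which one prevails.

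The baseline tests have a different weakness. With sound randomisation, every baseline difference arises by chance. The test asks a question whose answer is known, and a significant result on some variable gives a false signal.

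**Working it through.** The article states no power, effect size, SD or powered sample size, so it has no figure to reproduce.

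**Step 1. What each planned test contrasts**

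| Planned test | Contrast | Compares randomised arms on outcome? |
|---|---|---|
| Two-factor ANOVA, group × time | PAA v AA over three times | Yes |
| Chi-square at follow-up | PAA v AA, categorical outcomes | Yes |
| One-factor ANOVA within an arm | Visits within that arm | No |
| Baseline t-test and chi-square | PAA v AA before surgery | No |

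**Step 2. How often the within-arm tests disagree when the arms do not**

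Suppose both arms truly change equally, and each within-arm test has power p. The arms are independent, so P(exactly one significant) = 2p(1−p), and P(PAA only) = p(1−p).

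| p | Exactly one arm | PAA only |
|---|---|---|
| 0.05 (no change in either arm) | 2×0.05×0.95 = 9.5% | 4.8% |
| 0.30 | 2×0.30×0.70 = 42% | 21% |
| 0.50 (maximum) | 2×0.50×0.50 = 50% | 25% |
| 0.80 | 2×0.80×0.20 = 32% | 16% |
| 0.95 | 2×0.95×0.05 = 9.5% | 4.8% |
| 1.00 | 0 | 0 |

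**Step 3. The same check by simulation**

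There were 20,000 trials per setting, with three time points, alpha 0.05 and no true difference between arms. Assumptions not in the article: within-patient correlation 0.6, linear change reaching the stated number of SDs at the last visit, and 5, 20 or 40 patients per arm. Selected settings:

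| n per arm | True change (SD) | Within-arm power | Exactly one arm | PAA only |
|---|---|---|---|---|
| 5 | 0 | 5.0% | 9.5% | 4.8% |
| 5 | 0.5 | 13.9% | 23.7% | 11.9% |
| 5 | 0.8 | 29.6% | 41.2% | 20.6% |
| 5 | 1.2 | 59.5% | 48.6% | 24.3% |
| 20 | 0.5 | 56.9% | 49.1% | 24.8% |
| 20 | 0.8 | 94.0% | 11.3% | 5.6% |
| 40 | 0.3 | 44.3% | 49.2% | 24.0% |
| 40 | 0.8 | 99.9% | 0.1% | 0.0% |

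Across all settings run, the planned group × time test was falsely significant in 4.8% to 5.2% of trials. The between-arm test holds its level on the same data.

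**Step 4. Baseline tests**

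Under sound randomisation each test at 0.05 is falsely significant about 5% of the time. With eight independent tests (both the number and the independence are assumptions), P(at least one) = 1 − 0.95^8 = 34%.

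**Step 5. Baseline as a covariate rather than a level of time**

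With baseline as a level of time, the arm effect at a visit is read as a difference in mean change from baseline. With equal SD σ and correlation ρ, the variance of change is 2(1−ρ)σ². After adjustment for baseline the residual variance is (1−ρ²)σ². The ratio is (1+ρ)/2. At the assumed ρ = 0.6 this is 0.64/0.80 = 0.80, or 20% less variance, before allowing for estimation of the slope (which matters at five per arm). The gain vanishes as ρ approaches 1. The adjusted model also gives one estimate per follow-up visit, whereas the interaction test is a single test of whether the two time profiles are parallel.

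**The case against.** The strongest reply is that the article already assigns the arm comparison to the right kind of test. The group × time ANOVA comes just before the within-arm sentence, which addresses a different question, the course inside each arm. This stands. A reader might infer that the plan has no valid between-arm analysis, but the Analysis section contradicts that.

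A reader might also infer that the investigators intend to argue from one arm being significant and the other not. No sentence says so. The Discussion passage comes from a limitation about short follow-up and states a hypothesis of differential change, which is what group × time tests. The misreading is a risk, not a documented plan.

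It is tempting to quote only 42%, 50% and 32% and set them against a nominal 5%. That overstates the case. Those figures need within-arm power between 0.30 and 0.80. With no change in either arm the rate is already 9.5%, and if recovery is large for the sample size it falls towards 0. The false pattern in favour of PAA is half of each figure. No planned decision rule carries these error rates.

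Nor should the baseline t-test be faulted for low power at five per arm. If baseline differences are chance by design, there is no true difference to detect, and five per arm is the pilot only.

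Finally, removing every chi-square test would go too far. The same sentence covers follow-up, where chi-square is the only stated between-arm test for categorical outcomes.

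**Conclusion.** The point holds as a minor one. The plan attaches P<0.05 to within-arm and baseline tests that cannot answer its question and does not mark them as descriptive. With equal true change in both arms, exactly one arm is significant in 0 to 50% of trials, and PAA alone in 0 to 25%, depending on within-arm power. The article gives no figures from which that power could be fixed. The planned group × time test is not affected and held about 5% in simulation.

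The formula assumes independent arms with equal power. The simulation also assumes a within-patient correlation of 0.6 and linear change. The statement on baseline tests assumes that allocation was sound. The documents do not support a claim that the trial lacks a between-arm analysis, or that it will draw its conclusion from the within-arm results.

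**What to change.** - Replace the within-arm ANOVAs with mean change per arm and visit, with 95% confidence intervals and no P values.
- Present the baseline table by arm without P values. Drop the t-test and chi-square test at baseline only.
- Keep the chi-square comparison of the arms at follow-up for categorical outcomes.
- For continuous outcomes, base every PAA versus AA statement on the between-arm difference at four weeks and three months, with the baseline value as a covariate and not as a level of time. State that these results carry the treatment conclusion.

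The cost is a small change of model and of table format, so slightly more than wording. No new patients, visits or measurements are needed, because baseline values are already collected. The Trial status section gives recruitment as finished and the trial as being in statistical analysis, so the change of model should be recorded with its date and reported as a departure from the published plan.
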